### 2.3. Experimental Design

The study is designed as a one-year two-armed, randomized, controlled intervention trial (Figure 1). All participants were requested to sign a written informed consent after being informed about all study procedures and after adequate time for consideration. Group assignment was conducted, applying the minimization method [21]. Accordingly, all participants were stratified to the intervention or the control group (intervention: control = 1:1). Sex, age, maximum knee extension strength, dual task gait speed and peak oxygen consumption (VO2peak) served as strata for balanced group allocation. Couples were stratified to the same group due to infrastructural, motivational and interference issues. The number of couples was evenly balanced in both groups. Group assignment was communicated to the participants after baseline assessment via telephone. Participants of the intervention group receive two weekly training sessions for one year. The control group does not receive any treatments. Only a brief written recommendation for physical activity is sent out. They will be given the opportunity to take part in a training program once a week after the end of the study for 6 months. Both groups are to keep a logbook on falls, diseases/injuries and exercise over the entire one-year study period.

Primary and secondary endpoints are collected at pre- and post-testing. An additional interim test with only a few measurements is provided after six months of training. At baseline (T1) and at the post-assessment (T3) after one year, all measurements are performed. This includes neuromuscular, cognitive, cardiovascular and psychosocial tests. At the interim assessment (T2), only selected neuromuscular and psychosocial measurements are assessed for reasons of time and reasonableness. 

T1 also includes a medical anamnesis and physical examination to rule out some severe exclusion criteria in addition to the medical clearance. At T1 and at T3, three lab visits on non-consecutive days, each lasting one to two hours, are required for each participant. On day one, cardiovascular, pulmonary and sonographic assessments are completed. On day two, neuromuscular, cognitive and psychosocial measurements are conducted. On the third day of assessment, the Agility Challenge for the Elderly (ACE) takes place. The interim assessments (T2) are completed within 45 min.

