
### 2.9. Sample Size Estimation and Statistical Procedures

A sample size estimation was conducted with G*Power (Version 3.1, Heinrich Heine University, Duesseldorf, Germany). 68 participants (34 per group) are needed for statistical analysis, assuming moderate effects (f = 0.2) for training-induced changes in the primary outcomes (statistical power 90%, two-sided significance level α=.05). Expecting a realistic dropout rate of about 25%, a total of 85 participants were initially recruited.

Data entry will be double-checked and data ranges will be controlled for plausibility. Two researchers ([name]) will do data management and analysis. Independently conducted two-factorial repeated measured analyses of co-variance (rANOVA), with the respective endpoint as a baseline measure serving as the covariate [53], will be computed as primary analysis to assess the time course of adaptations between groups (factor 1: control group vs. intervention group; factor 2: time point of measurement; baseline, interim, post). The rANOVA interaction term between both factors is the main term of interest. Together with 90% confidence intervals, change scores from T1 to T3 and from T1 to T2 and T2 to T3 are calculated to arrive at an estimate of the size of the observed effects. The intention-to-treat analysis will be computed. The intention-to-treat analysis will be compared to as-treated analysis. Potential differences will be discussed.

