### 3.3. Potential Limitations and Risk for Bias

Participants were recruited from the general population via newspaper advertisement, which could lead to a selective recruitment of those older adults, that are intrinsically motivated to exercise and wo are already physically active. Group allocation was done according to the minimization method, which is comparable to a randomization method in smaller samples [21]. It allows us to balance important demographic measures and primary and secondary outcomes with possibly small group differences at baseline. Sex, age, maximum knee extension strength, dual task gait speed and VO2peak serve as strata for minimization, notably attenuating the risk of bias. Only participants who stated that they were willing to be randomized in one of the two groups could take part in the study to minimize dropout in the control group. Group preferences were strictly not allowed. Couples were randomized to the same groups. As is usual in exercise intervention studies, the blinding of participants is not possible. Due to personal and financial resources, the blinding of assessors and coaches is not possible either, which yields an acceptable risk for bias. Measurements are standardized and performed in the same room by the same assessor at T1, T2 and T3. Measurements are scheduled at the same time of the day for T1, T2 and T3 if possible. For each measurement domain, one gold-standard setter teaches all other assessors. The control group does not receive any treatments, but for ethical reasons they receive written recommendations for physical activity. Their potential autonomous exercise over the one-year period could influence the results of the study and is, therefore, captured via a logbook.

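### The primary model omits most of the factors used for minimisation, which forgoes a modest amount of precision if they are prognostic; the planned power is not eroded

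*Protocol article*

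**What the plan says.** Section 2.3 describes 1:1 allocation by minimisation and lists the factors: "Sex, age, maximum knee extension strength, dual task gait speed and peak oxygen consumption (VO2peak) served as strata for balanced group allocation". Section 3.3 repeats the list and relies on it as a safeguard; the five factors "serve as strata for minimization, notably attenuating the risk of bias".

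Section 2.9 specifies a two-factor repeated-measures analysis of covariance (group by time), "with the respective endpoint as a baseline measure serving as the covariate". It adds: "The rANOVA interaction term between both factors is the main term of interest". No other covariate is named anywhere in the article.

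The four primary endpoints are knee extension strength (Fmax), reactive balance, dual task gait speed and the ACE. Section 2.7 lists strength, gait speed and balance at the six-month interim assessment, but not the ACE.

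**The concern.** Minimisation makes the arms alike on the chosen factors, so these contribute less to the chance difference between arms than they would under simple randomisation. A model that leaves them out still counts the variation they explain as random error. If they are prognostic beyond the endpoint's own baseline, the standard error describes more chance imbalance than the design allows. The intervals are then somewhat too wide and the test somewhat conservative.

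The gap differs by endpoint. For reactive balance and the ACE, all five factors are absent. For Fmax and dual task gait speed, one of five enters as the endpoint's own baseline and four are absent.

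At stake is efficiency. The treatment estimate is not biased by the omission, and the omission does not raise the false-positive rate. With 79 people randomised and about 25% dropout expected, precision that costs no extra data is still worth having.

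**Working it through.** **1. The plan's own sample size.** Inputs from section 2.9: f = 0.2, power 90%, two-sided α = 0.05, N = 68. The number of time points m and the correlation ρ are not stated. For a within-between interaction F test with two groups, λ = N·f²·m/(1 − ρ), df1 = m − 1 and df2 = (N − 2)(m − 1). Assuming m = 2 and ρ = 0.5:

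- λ = 68 × 0.04 × 2 / 0.5 = 10.88, with 1 and 66 degrees of freedom; power = 0.9015, and 68 is the smallest even N that reaches 90%.
- With m = 3 and ρ = 0.5, N = 56 would suffice, and power at 68 is 0.956.

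So 68 is reproduced with no gain from any extra covariate.

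**2. Upper bound on the effect of omission.** Let R² be the share of variance, left after own-baseline adjustment, that the omitted factors explain. The article does not give it, so a range is assumed. With perfect balance, the ratio of model SE to true SE is 1/√(1 − R²), and type I error is 2·[1 − Φ(1.96/√(1 − R²))]:

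- R² = 0.10: ratio 1.05, type I 3.9%
- R² = 0.20: ratio 1.12, type I 2.8%
- R² = 0.30: ratio 1.20, type I 1.9%

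**3. Realistic minimisation.** Balance is in practice imperfect. Simulation: N = 68; minimisation on five two-level factors with assignment probability 0.8 (assumed); 3,000 runs per scenario; effect 2·√10.88/√68 = 0.80 residual SD. The outcome is a single follow-up value or contrast analysed by ANCOVA. Results for an endpoint whose baseline is not a minimisation factor (reactive balance, ACE):

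| Assumed R² | Model SE / true SD, baseline only | SE excess | Type I, baseline only | Power, baseline only | Power, factors added | Difference (points) |
|---|---|---|---|---|---|---|
| 0 | 0.244 / 0.242 | 0.8% | 4.7% | 89.6% | 88.9% | −0.7 |
| 0.05 | 0.244 / 0.238 | 2.5% | 4.6% | 89.4% | 90.0% | +0.6 |
| 0.10 | 0.244 / 0.238 | 2.5% | 4.8% | 90.9% | 91.5% | +0.6 |
| 0.20 | 0.244 / 0.235 | 3.8% | 4.2% | 91.1% | 94.9% | +3.8 |
| 0.30 | 0.244 / 0.227 | 7.5% | 3.7% | 92.4% | 96.6% | +4.2 |

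Simulation error is about 1.3% on each true SD (1/√(2 × 3,000)) and about 0.4 points on a 5% rejection rate (√(0.05 × 0.95/3,000)). The SE excess is therefore read as about 2% to 7%, and small differences between rows carry no weight.

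For an endpoint whose baseline is itself a minimisation factor (Fmax, dual task gait speed), the pattern is similar. Power moves from 91.2% to 91.5% at R² = 0.05 and from 92.4% to 96.6% at 0.30. At 0.30 the SE excess is larger (0.243/0.220, about 10%) and type I error is 2.8%. At R² = 0 power falls from 89.6% to 88.5%.

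**4. What reaches the group-by-time term.** Suppose covariate x has coefficient b1 at T1 and b3 at T3. A person's change then contains (b3 − b1)·x. If b3 = b1, x cancels and was never in the error of the interaction. If b3 ≠ b1, only an x-by-time term removes it. With complete data, x entered as a main effect alone leaves the interaction unchanged. A numerical check agrees: with 68 simulated people, complete data, a random-intercept model and five strongly prognostic covariates, the interaction estimate was 0.13141 (SE 0.35577) both with and without the five main effects. In step 3, R² must therefore be read as the share of the tested contrast, given own baseline, that the factors explain.

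**The case against.** The strongest objection is that the main term is an interaction, tested against within-person error. Sex, age or fitness may shift a person's level equally at every visit and say little about change. The true R² for the tested contrast may then be close to zero, and so may the loss. This stands: it limits the size of the point and determines the form of the fix. It does not justify omission, because adjusting costs only about 1 point of power at R² = 0.

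A reader might infer that power built into the design is being lost. The article does not support that. N = 68 is reproduced without any covariate gain (under m = 2 and ρ = 0.5), and baseline-only power stays between 89% and 92% in every simulated scenario. What is forgone is an unplanned gain.

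A reader might also infer that the standard errors are certainly too large, by 5% to 20%. Those figures need perfect balance, and every R² is assumed. The net direction is not settled either. Section 2.3 says "Couples were stratified to the same group due to infrastructural, motivational and interference issues", and the model names no couple term. Positive correlation within couples would make the standard error too small. The article does not give the number of couples. This is a separate issue, but it rules out calling the test conservative overall.

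The Abstract speaks of block randomisation. Sections 2.3 and 3.3, which describe the procedure, both say minimisation. Under block randomisation that ignored these factors, the conservatism would disappear, but adjusting for prognostic factors would still gain precision.

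Finally, a fuller analysis plan may add the factors. Section 2.9 nevertheless names the primary model and its covariate, so the choice is stated and not merely left open. If a fuller plan differs, section 2.9 should say so.

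**Conclusion.** The mismatch between allocation and analysis is real, and its consequence is modest. To the extent that the omitted factors predict the outcome beyond its own baseline, the model standard error is slightly conservative and some precision is given up.

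For reactive balance and the ACE, where the gap is fullest, an assumed R² of 0.05 to 0.30 gives a standard error about 2% to 7% too large, type I error of about 3.7% to 4.8%, and roughly 0.5 to 4 points of power forgone. At R² = 0 nothing is lost by omission. These figures rest on the assumed R², an assignment probability of 0.8, 68 people analysed, a single-contrast ANCOVA and independent participants. The planned 90% power is not eroded, and the omission itself introduces no bias.

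**What to change.** In section 2.9, add the five minimisation factors to the primary model for each primary endpoint: sex as binary, and age, knee extension strength, dual task gait speed and VO2peak as continuous T1 values. Do not enter the endpoint's own baseline twice. Then state how they enter:

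- Where the group-by-time interaction is tested, include each factor with its covariate-by-time term. Some software does this by default; the text should not rely on it.
- Where there is no interim measurement, as for the ACE, an ANCOVA on the T3 value with own baseline and the five factors is enough.
- Take the reported effect estimates and their intervals from the same adjusted model.

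If the factors are to stay out, give the reason in section 2.9.

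The cost is wording, plus four degrees of freedom (Fmax, dual task gait speed) or five (reactive balance, ACE) for each contrast tested. All five variables were needed for allocation, so no new data are required. How to handle couples should be decided separately.

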### 2.8. Intervention

The first training session takes place immediately after group allocation. Participants train in three separate groups with a maximum of 13 participants in each group. Two trained study assistants supervise all sessions. Each of the training groups train twice a week for one year with a two-week Christmas break. Training sessions are held at gyms, located at the campus of the German Sport University Cologne. The gyms are equipped with regular basic equipment (e.g., mats, cones, ropes, hoops). The sessions last for 60 min in total and consist of a diverse 10 min agility-specific warm-up, followed by a 45 min agility training and a 5 min cool-down. Training is accompanied by music in line with the preferences of the participants. The warm-up either consists of a series of instructed exercises, dance-like routines or exercises incorporating balls. The agility training part is divided into three to four stations that the participants attend in pairs or in small groups. The load duration is one minute, followed by one minute of rest with four to five repetitions at each station. In the last third of the one-year intervention period, more complex parkour settings are installed. The individual load duration exceeds one minute and the time for rest is longer. As briefly described in the introduction, agility training includes four components: start-stop, change-of-direction, balance and strength. In order to progressively design training sessions, the one-year intervention period is divided into three thirds. During the first third, two of the four agility components are part of each training session, alternating every second session. In the second third, three of four components are combined in every session and then, only in the last third, all agility components are simultaneously integrated in each session. The complexity of the training sessions is progressively increased by changing the physical, perceptual and/or cognitive loads of the exercises. The training design and progression are displayed in Figure 2. Participants are always pointed to potential hazards during the exercises (e.g., stumbling over mats, slipping on a cone). They are taught to give each other assistance, e.g., during balancing exercises. Any adjustment of the original training protocol as well as adherence for every session is documented in detail by the coach. For each session, participants are asked to state their overall rate of perceived exertion (BORG scale) immediately after the end of the session. Additionally, in each session, three to four randomly chosen participants wear heart rate sensors (polar, H7, Buettelborn, Germany) to exemplarily capture heart rates during the training. A participant does not continue the allocated intervention if he or she requests it or suffers pain or an injury. Adverse events are recorded and potential sources will be discussed and eliminated if necessary.

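### The repeated-measures ANOVA named as primary drops, in its classical form, anyone with a missed visit, which does not fit the intention-to-treat analysis promised beside it

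*Protocol article*

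**What the plan says.** All of the analysis text is in section 2.9 of the protocol article.

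- **Model.** The primary analysis is a two-factor repeated-measures analysis, called both analysis of covariance and rANOVA. The factors are group and time, time has three levels (baseline, interim, post), and the baseline value of the endpoint is the covariate. The group-by-time interaction is the term of main interest.
- **Analysis set.** "The intention-to-treat analysis will be computed", and it is to be compared with an as-treated analysis.
- **Size.** "68 participants (34 per group) are needed for statistical analysis". Then: "Expecting a realistic dropout rate of about 25%, a total of 85 participants were initially recruited".

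Three other places bear on the point. The Abstract reports 85 enrolled and 79 randomised after baseline testing, and says that all participants are tested before, after and at six months. Section 2.7 lists the interim measurements: leg extension strength, gait speed including dual task, and perturbed balance are there, and the ACE is not. Section 2.8 covers stopping the training: "A participant does not continue the allocated intervention if he or she requests it or suffers pain or an injury".

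**The concern.** A classical repeated-measures ANOVA works on one row per person with a value in every time column. A person with one empty column leaves the analysis, and any values that were measured go too. The analysis set is then the complete cases, whatever name it is given. An intention-to-treat analysis is meant to use the outcome data of everyone randomised, in the arm to which they were allocated.

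The trial runs for a year, expects dropout, and has one arm that trains twice a week. Pain and injury are among the section 2.8 reasons for stopping training, and they could plausibly be related to strength, balance and gait. If people who stop also miss a visit, the complete cases may differ from the randomised groups.

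The planned comparison with an as-treated analysis would not reveal this. If both analyses run on the same complete cases, agreement between them says little about the effect of dropout.

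**Working it through.** **Inputs.** From section 2.9: 68 needed, 85 recruited, about 25% dropout, "two-sided significance level α=.05", "statistical power 90"%, and "assuming moderate effects (f = 0.2) for training-induced changes in the primary outcomes". From section 2.3: allocation "intervention: control = 1:1". From the Abstract: 79 randomised. The article does not give the correlation between repeated measures or the number of measurements used for the sample size, so these are assumed below and a range is shown.

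**1. Reproduce the plan's 68.** For a within-between interaction with k = 2 groups and m measurements, λ = f²·N·m/(1 − ρ), df1 = (k − 1)(m − 1) and df2 = (N − k)(m − 1), taking sphericity to hold. With m = 2 and ρ = 0.5, λ = 0.04 × 68 × 2/0.5 = 10.88 on 1 and 66 df. Power is 0.9015 at N = 68 and 0.8926 at N = 66, so 68 reproduces. With the model's three time points and ρ = 0.5, the requirement is 56. For ρ from 0.3 to 0.8 it runs from 94 down to 30 (m = 2) or from 76 down to 24 (m = 3).

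**2. What the plan's figures imply for losses after randomisation.** The 85 equals 68 × 1.25. Six of the 85 were not randomised (85 − 79), so:

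| Reading | Left for analysis | Lost of the 79 randomised |
|---|---|---|
| The planned 68 remain | 68 | 11, or 11/79 = 13.9% |
| 25% of the 85 are lost | 85 × 0.75 = 63.75, about 64 | 15.25, or 15.25/79 = 19.3% |
| A further 25% of the 79 are lost (assumption, not the plan's figure) | 79 × 0.75 = 59.25, about 59 | about 20, or 25% |

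**3. What the named model does with incomplete records.**

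| Visits attended | Knee strength, reactive balance, dual task gait | ACE (not listed at T2) |
|---|---|---|
| T1, T2, T3 | kept | kept |
| T1, T3 (missed T2 only) | deleted, valid T3 value lost | no effect |
| T1, T2 (lost before T3) | deleted, valid T2 value lost | no T3 value in any case |
| T1 only | deleted | no T3 value |

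The second row is a loss that the model alone causes. The article gives no rate for it. As an assumption, if 5% to 10% of the 79 missed only T2, that is 0.05 × 79 = 4 to 0.10 × 79 = 8 people, on top of those lost before T3.

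The last column shows a side effect. With the ACE measured only at T1 and T3, the three-level model cannot be fitted to that endpoint as written.

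**4. Cost in power.** On the assumptions that reproduce 68 (m = 2, ρ = 0.5), power is 0.94 at N = 79, 0.90 at 68, 0.88 at 64, and 0.86 at 60 and at 59. With three measurements and the same ρ, it is 0.98, 0.96, 0.94, 0.93 and 0.92. The loss is modest. The main issue is which participants the estimate represents.

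**The case against.** The case on the other side has five parts.

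- **Exclusion is not stated.** Nothing in the article says that people with missing visits leave the intention-to-treat result. Imputation is not ruled out, and missing-data rules are commonly left to a full protocol or SAP, neither of which is shown. This stands: the silence is no finding. The point rests on the model that the article does name, which does not by itself deliver the analysis set that it promises.
- **Inflating for dropout is routine.** A reader might infer that sizing on 68 confirms that dropouts will be excluded. It does not. It shows only that losses are expected.
- **The 25% does not refer to the randomised.** A reader might infer that a quarter of the randomised, about 20 of 79, would be left out. Section 2.9 ties the 25% to the 85 recruited, and six of those were gone before randomisation.
- **Stopping training is not leaving the study.** Section 2.8 speaks of the allocated intervention only, and the Abstract says that all participants are tested. Testing of those who stop may already be intended.
- **The direction of bias is open.** A reader might infer bias towards the training arm. For example, if a quarter of that arm stopped with no benefit, completers gained 0.5 SD and no controls were lost, the as-randomised effect would be 0.75 × 0.5 = 0.375 SD, and the completer figure would be one third too high. The article supports none of these assumptions. It gives no dropout by arm, and section 3.3 shows concern about dropout among controls. A mixed model alone would not generally recover 0.375 SD if those who stopped had no follow-up values. If they were tested at both visits, the ANOVA would include them too.

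These arguments limit the claim, but they do not remove the mismatch between the named model and the promised analysis set.

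**Conclusion.** The point holds as a mismatch within section 2.9. Taken in its classical form, the primary model is a complete-case analysis, and for three of the four primary endpoints it would throw away one-year results from people who missed only the six-month visit. On the plan's own figures, 13.9% to about 19% of the 79 randomised may be lost. T2-only misses would come on top, at a rate that the article does not give.

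This conclusion assumes that no imputation or likelihood-based fitting is specified elsewhere. If it is, one sentence in the analysis text settles the matter. The article does not support a stated size or direction of bias. The change should be made before analysis, and because the trial was still running when the article was written, there was time for it.

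**What to change.** 1. **Primary model for knee extension strength, reactive balance and dual task gait speed.** Use a likelihood-based mixed model for repeated measures with T2 and T3 as outcomes, the baseline value as covariate, and group, time and group-by-time terms. Include every randomised participant with any post-baseline value, as allocated. With baseline as a covariate only, the interaction tests whether the group difference changes between T2 and T3. The training effect should therefore be read from the model's group difference at T3, and at T2 for the six-month question.
2. **ACE.** Use a baseline-adjusted group comparison at T3.
3. **Follow-up.** State that participants who stop training are still tested at T2 and T3 and stay in the analysis. This step protects against selective loss in a way that the choice of model cannot.
4. **Sensitivity.** Show the complete-case repeated-measures ANOVA as a sensitivity analysis only.

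The cost is a few sentences and minor extra analysis work. The T2 and T3 visits are already scheduled for everyone. The mixed model relies on data being missing at random, and people with no post-baseline value still contribute nothing, so their number should be reported by arm.
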